# Efficacy of belimumab combined with rituximab in severe systemic lupus erythematosus: study protocol for the phase 3, multicenter, randomized, open-label Synbiose 2 trial

**DOI:** 10.1186/s13063-022-06874-w

**Published:** 2022-11-12

**Keywords:** Systemic autoimmune disease, Systemic lupus erythematosus, Lupus nephritis, Belimumab, Rituximab, Clinical trial

## Abstract

**Background:**

Belimumab, an anti-B-cell activating factor antibody, is approved for the treatment of auto-antibody positive systemic lupus erythematosus with a high degree of disease activity. Anti-CD20 B cell depletion with rituximab is used in refractory SLE as well, although with variable responses. We hypothesized that incomplete B cell depletion, related to a surge in BAFF levels following rituximab treatment, can cause ongoing disease activity and flares. The Synbiose 1 study primarily focused on immunological effects and shows the preliminary clinical benefit of combined rituximab and belimumab in SLE. The Synbiose 2 study will evaluate the clinical efficacy of combining belimumab with rituximab in patients with severe SLE, allowing the tapering of prednisolone and mycophenolate.

**Methods:**

Synbiose 2 is a phase 3, multicenter, randomized, controlled, open-label 2-year clinical trial. Seventy adults with severe SLE including lupus nephritis will be randomized 1:1 to receive either standard of care consisting of prednisolone and mycophenolate as induction and maintenance treatment, or belimumab and rituximab combined with standard of care as induction treatment, followed by prednisolone and belimumab as maintenance treatment. The primary objective is to assess whether combined B cell therapy will lead to a reduction of treatment failure. Secondary endpoints are complete and partial clinical and renal response and the improvement of SLE-specific autoimmune phenomena. Safety endpoints include the incidence of adverse events, with a special interest in infections.

**Discussion:**

The Synbiose 2 trial is the first multicenter phase 3 clinical trial investigating combined B cell targeted therapy in SLE, including lupus nephritis. The outcome of this study will provide further evidence for the clinical efficacy of this new treatment strategy in severe SLE.

**Trial registration:**

ClinicalTrials.gov NCT03747159. Registered on 20 November 2018.

## Strengths and limitations of this study

◦ This is a randomized, controlled phase 3 trial with 2 years of follow-up, focusing specifically on patients with severe SLE including lupus nephritis◦ This study’s hypothesis was built on a strong scientific basis of preclinical and clinical studies of belimumab and rituximab used as single agents as well as combined in SLE patients◦ The design includes tapering of mycophenolate and prednisolone as maintenance therapy in the intervention group◦ This study compares two different treatment strategies rather than a single add-on, placebo-controlled agent, which could be perceived as a limitation. However, this set-up is closely related to clinical practice making the outcomes directly translatable to patient care◦ The study is limited by its open-label design

## Introduction

Systemic lupus erythematosus (SLE) is a chronic autoimmune disease in which the loss of tolerance to nucleic acids and their binding proteins results in the generation of autoantibodies that initiate and propagate tissue-damaging inflammation involving every organ system. Many patients require life-long immunosuppression, often with high-dose corticosteroids, cyclophosphamide, or mycophenolate mofetil, non-specifically targeting the immune system to reduce inflammation. This results in low-level disease activity in only 25–44% of patients in the long term, while sustained complete remission is rare [1–4]. Moreover, approximately 10% of lupus nephritis (LN) patients develop end-stage renal disease in 5 years, increasing to over 20% in 15 years [5]. Side effects of the current treatment strategies are (opportunistic) infections in the short term and risk for malignancy and cardiovascular disease in the long term, contributing to the reduced life expectancy of SLE patients [6, 7]. This substantiates the need for developing better strategies to prevent and treat the sequelae of SLE.

Treating SLE patients with biologicals is attractive because they have the potential to specifically target key culprits in the pathogenesis of SLE, possibly increasing efficacy and reducing the risk for infections or malignancies as compared to conventional immunosuppressants. Rituximab is a B cell-depleting anti-CD20 monoclonal antibody that has shown efficacy in several retrospective and open-label studies [8–17]. However, two phase 3 double-blind, placebo-controlled trials were unable to meet their primary endpoints, limiting its clinical use to off-label treatment of refractory SLE only [18, 19]. Post hoc analysis in LN patients demonstrated that depth of B cell depletion was associated with complete renal response upon rituximab treatment, suggesting that a more profound B cell depletion yields better clinical outcomes [20]. This premise was corroborated by a recent positive phase 2 study with obinutuzumab, a novel anti-CD20 monoclonal antibody therapy characterized by improved B cell depletion [21].

Another explanation for the variable efficacy of rituximab is its association with elevated levels of B cell activating factor (BAFF, also known as BLyS). BAFF is a cytokine necessary for the survival, activation, and differentiation of B cells to plasma cells and the integrity of germinal centers. BAFF levels are elevated in SLE and are associated with disease activity and flares [22–25]. Upon rituximab-induced B cell depletion, increased BAFF levels are observed which can be capable of triggering a feedback loop of B and T cell activation resulting in a surge of the humoral autoimmune response [26, 27]. In a cohort study, this was reflected by a rise in anti-double-stranded DNA (anti-dsDNA) levels and relapse [28]. These observations suggest that the clinical efficacy of anti-CD20 mediated B-cell depletion can be increased by the addition of a BAFF-inhibiting agent.

Belimumab—a recombinant monoclonal IgG1λ antibody that antagonizes circulating BAFF—was approved as add-on therapy in adults with active, auto-antibody positive SLE with a high degree of disease activity despite standard therapy, after the results of two pivotal phase 3 clinical trials and a subsequent trial for LN [29–31]. Despite showing superior efficacy compared to standard of care, belimumab alone as add-on therapy was not able to achieve more than 30% complete renal response in LN. The Synbiose 1 (*Synergetic B cell immunomodulation in SLE*) study was the first to comprehensively describe the clinical and immunological effects of combining rituximab and belimumab in a cohort of patients with severe, refractory SLE [27, 32, 33]. From this study, we have learned that combining rituximab with belimumab was safe and well-tolerated with clinically relevant positive responses. Briefly, Synbiose 1 demonstrated that long-term belimumab treatment restrained full B cell repopulation leading to long-lasting reduction of anti-dsDNA, anti-C1q and ENA autoantibodies, and neutrophil extracellular traps (NETs). In 67% of highly treatment-refractory patients, clinical response was observed, of which 80% continued belimumab maintenance treatment during the 2-year follow-up, allowing discontinuation of mycophenolate, and tapering of corticosteroids to 7.5mg or less. Subsequently, CALIBRATE and BEAT-LUPUS have conformed in randomized phase 2 studies that the combination of belimumab and rituximab is safe and achieves relevant immunological and clinical endpoints in refractory SLE and LN patients [34, 35]. These studies showed suppressed B cell repopulation and enhanced negative selection of autoreactive B cells, lower anti-dsDNA levels, and reduced risk of severe flares upon combined B cell therapy. Collectively, these studies have prompted us to conduct the Synbiose 2 study, a phase 3 randomized study to investigate the long-term efficacy and safety of belimumab combined with rituximab in severe SLE patients.

## Methods

### Study design

This is a phase 3, multicenter, randomized, controlled, open-label, noninferiority 2-year study conducted in The Netherlands, investigating the efficacy and safety of belimumab combined with rituximab. A list of participating academic and non-academic hospitals can be found on www.clinicaltrials.gov.

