### Sample size calculation

The power analysis to determine sample size of the study was based on data from the Synbiose 1 trial (i.e., combination treatment with belimumab and rituximab) and the ALMS trial (i.e., standard of care with mycophenolate and steroids) [32, 38]. To show a significant reduction in treatment failure, we assumed a treatment failure rate during the study period of 104 weeks of 54% in the standard of care group (in accordance with ALMS study results) compared to 23% in the intervention group (in accordance with the Synbiose 1 study results). We calculated that in order to demonstrate a hazard ratio of 2.97 with at least 80% power, using an alpha error confidence level of 5% and beta probability of 0.20, the study would require a total of 70 patients to be randomized with 35 patients in each group.

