## Discussion

This investigator-initiated trial was developed through analysis of clinical and immunological data of SLE patients using a combination treatment with rituximab and belimumab, a targeted and immunologically synergistic treatment for which there is great promise in autoantibody-mediated disease such as SLE and LN. The Synbiose 2 study will compare efficacy of two treatment strategies—standard of care alone versus standard of care and additional belimumab and rituximab—by assessing treatment failure over the study period of 2 years. Subsequently, the study will allow investigation of the potential improvement of targeting autoreactive B cells by starting treatment with subcutaneous belimumab followed by rituximab, and study the immunological effects on B-cell depletion and repopulation, circulating autoantibodies and NET formation. Ultimately, by evaluating the ability to reduce cumulative steroid dose and rapidly tapering mycophenolate while avoiding a flare of disease activity, this study addresses the clinical problem of long-term immunosuppressant toxicity as well as specifically targeting the humoral autoimmune responses in SLE patients. As such, the use of combined B cell targeted therapy may be thus be supported even in the case of equal efficacy to established treatment strategies.

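### The noninferiority label in the study design contradicts a superiority objective, sample size and test, and a non-significant result would not show equal efficacy

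*Protocol article*

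**What the plan says.** The Study design section of the protocol article calls the trial a "randomized, controlled, open-label, noninferiority 2-year study conducted in The Netherlands". The abstract's design line leaves that word out: "Synbiose 2 is a phase 3, multicenter, randomized, controlled, open-label 2-year clinical trial".

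The other statements that define the primary comparison point to superiority:

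- Objective (abstract, Methods): "The primary objective is to assess whether combined B cell therapy will lead to a reduction of treatment failure".
- Sample size calculation: the aim is given as "To show a significant reduction in treatment failure", with assumed 104-week failure of "54% in the standard of care group" and "23% in the intervention group", a hazard ratio of 2.97, 80% power and a 5% alpha.
- Statistical analysis: the difference between the groups in treatment failure is assessed with a log-rank test. Intention-to-treat is the primary population, and a per-protocol analysis is planned for immunological endpoints only.

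The Discussion, after describing lower cumulative steroid dose and rapid mycophenolate tapering, says that the combination may be "supported even in the case of equal efficacy to established treatment strategies".

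**The concern.** Superiority and noninferiority are different primary hypotheses with different rules for success. Under superiority, a log-rank test that does not reach significance leaves the question open. Under noninferiority, the conclusion depends on whether a confidence bound excludes a margin fixed in advance. One article cannot hold both for the same endpoint without saying how they relate.

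What is at stake is how a non-significant result may be read. The label, taken together with the Discussion's remark on equal efficacy, leaves room to present such a result as support for the combination. Whether 70 patients could carry that reading can be calculated.

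**Working it through.** **1. Reproduce the plan's own figure.** Inputs from the Sample size calculation: failure 54% and 23%, alpha 5%, power 80%, 35 per arm. The article does not state whether alpha is one- or two-sided; two-sided is tried first.

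- Hazard ratio = ln(1 − 0.54) / ln(1 − 0.23) = 2.97, as stated.
- Schoenfeld events, two-sided 5%: 4 × (1.96 + 0.84)² / (ln 2.97)² = 26.5, rounded up to 27.
- Mean failure probability = (0.54 + 0.23) / 2 = 0.385. Total N = 27 / 0.385 = 70.1, or 70 in two equal arms.
- Power at 70 × 0.385 = 26.95 expected events: 80.7%.

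The Freedman formula gives 32 events and about 83 patients two-sided, or 26 events and about 68 patients one-sided. All of these are superiority formulas, and none contains a margin. The stated 70 is therefore explained in full by a superiority design.

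**2. What 35 per arm could say if the arms were truly equal.** The article states no margin, so those below are assumptions. The two rates in the Sample size calculation serve as the range for a common failure rate p.

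- Standard error of the difference: SE = √(2p(1 − p)/35).
- Half-width of the 95% confidence interval: 1.96 × SE.
- Chance of excluding an excess of m (one-sided 2.5%): Φ(m/SE − 1.96).
- Smallest margin with 80% power: (1.96 + 0.84) × SE.
- Total N for 80% power at margin m: 2 × 2p(1 − p)(1.96 + 0.84)²/m², with each arm rounded up.
- Confidence interval around an observed hazard ratio of 1 with E = 70p events: exp(±1.96 × 2/√E).

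| | Both arms 54% | Both arms 23% |
|---|---|---|
| SE | 0.119 | 0.101 |
| 95% CI half-width | 23 points | 20 points |
| Chance of excluding 10 points | 13% | 17% |
| Chance of excluding 15 points | 24% | 32% |
| Chance of excluding 20 points | 39% | 51% |
| Margin with 80% power | 33 points | 28 points |
| Total N for a 10-point margin | 780 | 558 |
| Total N for a 15-point margin | 348 | 248 |
| Total N for a 20-point margin | 196 | 140 |
| Events; 95% CI around HR = 1 | 37.8; 0.53 to 1.89 | 16.1; 0.38 to 2.66 |

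For scale, the whole benefit assumed in the sample size is 54 − 23 = 31 points, which lies inside the 28 to 33 points that the trial could exclude with 80% power.

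**3. What changes if the combination is truly better.** Here SE = √((p₁(1 − p₁) + p₂(1 − p₂))/35), and the true advantage is added to m.

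- 54% against 23%: SE = 0.110. The chance of excluding a 10-point excess is Φ(0.41/0.110 − 1.96), about 96%.
- 54% against 34% (an assumed intermediate case): SE = 0.116. The chance is Φ(0.30/0.116 − 1.96), about 73%, for 10 points and about 85% for 15 points.

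The weakness in step 2 thus applies when the arms are equal or nearly so, which is the situation that the Discussion sentence addresses.

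**The case against.** The strongest reply is that the operative design is not in doubt. The label occurs once, in a descriptive sentence, while the objective, sample size and test all agree on superiority, so it may simply be a stray word that changes neither N nor the analysis. That may well be its origin. It still stands in the Methods as a statement of the trial's hypothesis, and it bears on what a non-significant result may be said to mean.

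The second reply is that the Discussion sentence is conditional and rests on lower steroid and mycophenolate exposure. It argues what would follow if efficacy were equal and sets no rule of inference. This is correct. A reader might infer that the sponsor intends to report a non-significant test as noninferior, or that the trial in effect cannot fail. The article says neither, and a clearly worse result would still count against the combination.

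Third, a margin may exist in the full protocol or analysis plan, neither of which is shown. Its absence from the article is therefore no finding in itself. A margin elsewhere would nevertheless not reconcile the label with the superiority objective, sample size and test printed here.

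Fourth, a reader might conclude that 70 patients can never support noninferiority. That is too broad: under a true advantage of the size assumed in the plan, power to exclude a 10-point excess is high.

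**Conclusion.** The concern holds as an internal contradiction about the primary hypothesis: one section says noninferiority, while the objective, sample size and primary test say superiority. The sample-size arithmetic is not in dispute.

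The equal-efficacy reading that the label and the Discussion leave open cannot rest on a non-significant log-rank test. With equal true failure anywhere from 23% to 54%, the data would be compatible with differences of roughly 20 points or more in either direction. The result assumes a normal approximation for the difference in proportions, 35 evaluable patients per arm, a one-sided 2.5% bound and margins chosen for illustration. The documents do not support going further, to a claim that a null result will be misreported or that noninferiority is out of reach whatever the true effect.

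**What to change.** - Delete the word noninferiority from the Study design section and state that the primary hypothesis is superiority of the combination in reducing treatment failure.
- State that a non-significant primary result is inconclusive and is not evidence of equal efficacy, and that the effect will be reported with its 95% confidence interval.
- Tie the Discussion sentence on equal efficacy to the excess of failures that this interval excludes.
- If noninferiority is truly intended, fix and justify a margin and a confidence-bound rule before database lock, and state what 70 patients can exclude.

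The main change costs wording only: 70 patients and the log-rank test stay as they are. The sponsor gives up an equal-efficacy claim that the design does not support.

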### Study population

The study will include adult SLE patients with severe disease with major organ involvement, including LN. In brief, patients are above 18 years of age and have a clinical diagnosis of SLE according to the Systemic Lupus International Collaborating Clinics (SLICC) criteria. Severe disease is defined as either an SLE disease activity index (SLEDAI) ≥ 12, new or progressive activity in major organ systems, or otherwise high disease activity despite conventional immunosuppressive treatment, which requires remission induction therapy. Detailed in- and exclusion criteria are summarized in Table 1.

**Table 1 Tab1:** Entry criteria. In- and exclusion criteria of the Synbiose 2 study

Inclusion criteria	Exclusion criteria
• ≥ 18 years of age • Having a clinical diagnosis of SLE according to the SLICC criteria 2012 • Severe, active SLE defined as one or more of the following: ◦ SLEDAI ≥ 12 ◦ New or worse SLE-related activity in major organs, i.e., CNS-SLE (includes NPSLE), vasculitis, nephritis, pericarditis and/or myocarditis, myositis, thrombocytopenia (< 60 × 10^9^/L), hemolytic anemia (Hgb < 4.4mmol/L = 7.0 g/dL) ◦ High disease activity that requires or warrants induction treatment by switching to or increasing dosage of oral mycophenolate • New, persisting or progressive disease activity despite the use of conventional maintenance immunosuppressive treatment (e.g., mycophenolate or azathioprine) • Confirmed positive SLE-specific autoantibodies defined as one or more of the following: ◦ ANA titer ≥ 1:80 ◦ Either 2 positive test results from independent time points within the study screening period, or one positive historical test result and 1 positive result during the screening period ◦ Anti-dsDNA serum antibody ≥ 30 IU/mL ◦ Either 2 positive test results from independent time points within the study screening period, or one positive historical test result and 1 positive result during the screening period	• Female patients who arepregnant or breastfeeding • Significant hypogammaglobulinemia (IgG < 4.0 g/L) or IgA deficiency (IgA < 0.1 g/L) • Immunization with a live vaccine within 1 month preceding day 0 • Active infection, defined as one or more of the following: ◦ Hospitalization for treatment of infection within 60 days preceding day 0 ◦ Use of parenteral antimicrobial agents within 60 days preceding day 0 ◦ Serological evidence of viral hepatitis defined as: patients positive for HbsAg or HbcAb, or hepatitis C antibody positivity, not treated with antiviral medication • Having a historically positive HIV test or test positive at screening • Having a history of a primary immunodeficiency • Having a neutrophil count of < 1.5 × 10^9^/L • Having a significant infection history that in the opinion of the investigator makes the candidate unsuitable for the study • Having a history of an anaphylactic reaction to parenteral administration of contrast agents, human or murine proteins or monoclonal antibodies • Having any other clinically significant abnormal laboratory value that in the opinion of the investigator makes the candidate unsuitable for the study • Drug or alcohol abuse or dependence within 1 year preceding day 0 • Having an active malignant neoplasm or one in the last 5 years, except basal cell or squamous cell carcinoma of the skin treated with local resection only, or carcinoma in situ of the uterine cervix treated locally and with no evidence of metastatic disease for 3 years • Having evidence of serious suicide risk, including suicidal behavior in the last 6 months and/or any suicidal ideation in the last 2 months

### Randomization

Seventy patients will be randomized 1:1 to one of two treatment strategies by computer-generated allocation in blocks, to either standard of care, consisting of corticosteroids plus mycophenolate as induction and maintenance therapy, or the intervention group where induction therapy consists of standard of care with the addition of belimumab and rituximab, and maintenance therapy of low-dose prednisolone and belimumab. Enrolment and randomization will be performed by the patient-treating physician researcher or primary investigator of the study center and are done as soon as possible after screening and obtaining informed consent, ideally before initiation of remission induction treatment, with a maximum of 4 weeks thereafter.

### Study treatments

All patients will be given standard of care consisting of 3 pulses of 500 mg (< 60 kg) or 1000mg (> 60 kg) of intravenous methylprednisolone. This will be followed by tapered oral prednisolone at a starting dose of 60mg daily together with mycophenolate at a starting dose of 500mg twice daily and increased weekly, titrated to achieve a target AUC of 60-90mg*h/L, with a maximum dose of 4000mg per day. In cases where therapeutic drug monitoring (TDM) is not possible, mycophenolate dose will be titrated against leukocyte counts and tolerability of the patient. Patients randomized to the intervention group will receive standard of care combined with self-administered subcutaneous belimumab 200mg weekly, and two doses of 1000-mg intravenous rituximab 4 and 6 weeks after belimumab initiation. One hundred-milligram intravenous methylprednisolone, 2-mg intravenous clemastine, and 1000-mg oral acetaminophen will be administered prior to rituximab infusions.

In both treatment groups, oral prednisolone will be tapered to 7.5mg before week 28 and to 5mg before week 52 and will be continued at a low dose for the remaining study period. Dose reduction to zero can be personalized to the tolerance of the patient, judged by the treating physician. In the control group, mycophenolate will be reduced by 50% at week 28 and continued for the remainder of the study period. In the intervention group, mycophenolate dose will be reduced by 50% at week 16 and discontinued at week 28. Belimumab will be continued throughout the entire study period. Consequently, after week 28, patients will enter the maintenance phase where they will receive either prednisolone and mycophenolate (control group) or prednisolone and belimumab (intervention group) (Fig. 1). Patients will be monitored closely during the study, with laboratory evaluation and study visits every 2 weeks during the first 8 weeks after inclusion, and increasingly longer intervals during the remainder of the study, up to 2 months eventually. An overview of study visits and assessments per visit is summarized in Table 2.

